### Study Aim and Objectives

In this study, we present the protocol for a 31-month SW-CRT trial. Our aim is to evaluate the performance of the SurgeCon platform in improving important patient and service process outcomes in EDs in an RHA in Newfoundland and Labrador and develop strategies to promote its scalability, sustainability, and successful implementation across the Canadian health system. The primary objective of the trial is to evaluate the effects of SurgeCon on ED performance by assessing its impact on LOS, PIA, and LWBS. The secondary objective of the trial is to assess the intervention’s impact on patient satisfaction and patient-reported experience with ED wait times and its ability to create better-value ED services by reducing ED costs.

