### Study Population

All individuals who visited any of the 4 selected EDs during the study period will be included in the collection of deidentified health administrative data. We will also collect and monitor ED-level key performance indicator (KPI) data such as LOS, PIA, and LWBS because they are impacted by patient volume. Patients who receive care at these EDs will be randomly selected for subsequent follow-up after they are discharged to collect information related to their experience in the ED and to determine their level of satisfaction with the care that they received.

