### Data Collection and Monitoring

Aggregate- and individual record-level data will be analyzed over the course of the study period to assess the effect of the intervention on patient outcomes, health service efficiency, and the cost of providing emergency care. Our analysis will include aggregate KPI data, record-level health administrative data, and aggregate financial data and will be provided to the research team by the Newfoundland and Labrador Centre for Health Information. The ED KPIs (ie, LOS, PIA, and LWBS) used as the primary outcomes for this study are further described in Table S1 in Multimedia Appendix 1 alongside other variables that will be used for statistical modeling. Each of the primary outcomes will be calculated and assessed monthly over the course of the study period. The total number of monthly ED visits will be used as the denominator for our cluster-level summaries.

Individual record-level health administrative data will include demographic variables (eg, sex, date of birth, and postal code), mortality data, wait times data, diagnosis data, and triage acuity scores, among other variables. These data will be used to create aggregate KPI and financial data provided by Newfoundland and Labrador Centre for Health Information and to assess the intervention’s impact on the type and volume of patients who visit one of the 4 selected ED sites during the study period. Financial data will capture expenditures for staff, supplies, and procedures originating from the ED and will include data related to pharmacy, diagnostic imaging, laboratory testing, surgical day care, operating room procedures, physician salaries, physician fees for service claims, nurse salaries, administrative staff salaries, ambulance services, and other related ED costs.

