The primary method of analysis used in this study is GLMM, which will consider monthly cluster-level summary measures such as means of LOS, PIA, or proportion of LWBS. Our GLMM models will include fixed effects for time, intervention effects, random effects, and random time effects for each cluster. In addition, ED setting (rural or urban), ED volume, and size of ED administrative resource will be added as cluster-level covariates. For secondary outcomes such as patient-reported experience and satisfaction, our individual-level GLMM models will include fixed effects for time, intervention effect, and random effects and random time effects for each cluster, with the covariates consisting of age, gender, the reason for ED visit, and cluster-level LOS, PIA, and proportion of LWBS.

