**Restructure ED^a^ organization and workflow**		
	Stable patient priority setting	Canadian EDs have been using the CTAS^b^ since 1999 [57]. What the SurgeCon intervention proposes is to augment CTAS by combining CTAS scores and waiting times to best meet the suggested time frame set out by the CTAS organization. Patients who are CTAS level 1 (resuscitation) or 2 (emergent) who are not stable will still be treated immediately in this model, but individuals who are less urgent (CTAS 3-5) will be treated when the CTAS 1-2 individuals become more stable, but before they are discharged. This allows the physician to quickly treat and discharge less urgent individuals before returning to spend more time with the urgent cases. This prioritization method can significantly improve patient flow without having to compromise patient safety.
	Door-to-door focus	A number of studies have found a strong correlation between patient satisfaction and PIA^c^; the shorter the PIA, the more satisfied the patient [58,59]. To reduce the time to PIA, we will use the following strategies: ED physicians and frontline providers will triage with nursing staff with the goal of increased patient discharge from the fast-track area or triage room without waiting. Triage nurse–driven orders (eg, symptom management, laboratory testing, and diagnostic imaging) will only be applied on patients who would be waiting longer than 1 hour to see a physician. If the patient can be seen by a physician within an hour, waiting for potentially unnecessary test results could delay the PIA. ED physicians will review patients arriving on ambulance stretchers in the hallway if there are no available beds instead of waiting for a bed to be free.
	Nurse practitioner–physician communication	SurgeCon reorganizes the traditional Canadian ED communication structure by promoting communication between NPs^d^, ERPs^e^, and RNs^f^ to work collaboratively to improve patient flow through appropriate allocation of patients. By opening lines of communication between NPs, ERPs, and RNs, the entire ED can work in unison to move patients further along their path to being discharged.

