**Establish a patient-centered ED environment**		
	Improve the overall appearance of physical spaces in the ED (eg, waiting room, fast-track zone, examination rooms, and treatment space) to improve patient satisfaction	This will be conducted in collaboration with Eastern Health. In consultation with our local patient partners, we will renovate, redecorate, and declutter ED spaces, removing outdated or irrelevant wall postings. All subsequent wall postings will require departmental approval and will be placed in a central location.

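### The satisfaction and patient-experience model adjusts for LOS, PIA and LWBS, so its intervention coefficient leaves out the part of SurgeCon's effect that runs through waiting

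*Protocol article*

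**What the plan says.** All references are to the Protocol article.

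- Study Aim and Objectives sets the primary objective as "assessing its impact on LOS, PIA, and LWBS". The secondary objective includes the intervention's "impact on patient satisfaction and patient-reported experience with ED wait times".
- Statistical Analysis, Analyses, gives the individual-level model for satisfaction and experience: time, intervention, random cluster and cluster-time effects, "with the covariates consisting of age, gender, the reason for ED visit, and cluster-level LOS, PIA, and proportion of LWBS".
- Table 1, door-to-door focus, cites a correlation between PIA and satisfaction ("the shorter the PIA, the more satisfied the patient") and then lists strategies to shorten PIA.
- Table 1 also has a component that does not act through waiting: "we will renovate, redecorate, and declutter ED spaces".
- Data Collection and Monitoring has LOS, PIA and LWBS calculated monthly through the study. The covariate list does not state its own timing, but monthly is the only form the article defines.
- Nowhere is the satisfaction model called a mediation or direct-effect analysis, and no companion model without the three indicators is given.

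**The concern.** A covariate that the intervention is meant to change lies on the path from intervention to outcome. Holding it fixed removes whatever part of the effect travels along that path. Here the three covariates are what SurgeCon is built to improve, and one of the outcomes is experience of waiting itself. The coefficient would answer whether patients are more satisfied at the same LOS, PIA and LWBS. The objective asks whether SurgeCon changes satisfaction.

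The better SurgeCon works on waits, the less this model can show of a benefit for patients. A real gain in satisfaction could be reported as no effect, and the covariate list would be the cause.

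**Working it through.** **The plan's figure.** Sample Size gives 11 surveys per month per hospital: 11 × 30 × 4 = 1,320, which reproduces. The 11 itself cannot be derived, because the 30% change it targets has no SD or baseline. The checks below are therefore in SD units.

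**Precision without the three indicators.** Inputs: 4 sites, 30 months, one crossover every 6 months after a 6-month baseline, n = 11 per site-month, ICC 0.1, two-sided 5% (sidedness assumed). The Hussey–Hughes variance is

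Var = I·s²(s² + T·t²) / [(I·U − W)s² + (U² + I·T·U − T·W − I·V)t²]

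- I = 4, T = 30, s² = 0.9/11 = 0.0818, t² = 0.1
- U = 24 + 18 + 12 + 6 = 60
- W = 6 × (0 + 1 + 4 + 9 + 16) = 180
- V = 24² + 18² + 12² + 6² = 1,080
- Numerator: 4 × 0.0818 × 3.0818 = 1.0086
- Denominator: 60 × 0.0818 + 1,080 × 0.1 = 112.909
- SE = √(1.0086/112.909) = 0.0945 SD
- Effect detectable with 80% power: (1.960 + 0.842) × 0.0945 = 0.265 SD

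**What the specified model targets.** Let m be the share of the total effect that runs through waits. The article gives no value for m, so a range is shown. The coefficient targets (1 − m) × 0.265, and power = Φ(δ/SE − 1.96) + Φ(−δ/SE − 1.96), with the SE held at 0.0945.

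| m | target δ (SD) | δ/SE | power |
|---|---|---|---|
| 0% | 0.265 | 2.80 | 80% |
| 25% | 0.199 | 2.10 | 56% |
| 50% | 0.132 | 1.40 | 29% |
| 75% | 0.066 | 0.70 | 11% |
| 100% | 0 | 0 | 5% (the type I error rate) |

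These are upper limits, because adjustment also raises the SE.

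**Collinearity.** Background gives pilot means and SDs. The SDs are taken here as month-to-month SDs (an assumption). With half the site-months treated (60 of 120), R² = 0.25d² / (0.25d² + mean of the two variances) and VIF = 1/(1 − R²).

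- PIA: d = 104.3 − 42.2 = 62.1; 964.1/(964.1 + 81.8) = 0.92; VIF 12.8
- LOS: d = 199.4 − 134.4 = 65.0; 1,056.3/(1,056.3 + 246.2) = 0.81; VIF 5.3
- LWBS: d = 12.1 − 4.6 = 7.5; 14.06/(14.06 + 3.87) = 0.78; VIF 4.6

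**Both effects together.** A simulation (400 runs per scenario) fitted site and month effects with and without the three indicators. It assumed a total effect of 0.30 within-site SD, with the waiting route running through PIA. Without the indicators the estimate was about 0.30 and the SE 0.10 to 0.11. This agrees with the formula: 0.0945/√0.9 = 0.0996 on the within-site scale. Unadjusted power was 0.83 to 0.85 at pilot-sized indicator changes and 0.73 to 0.82 at 30% of them. With the indicators:

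| share bypassing waits | pilot-sized changes: estimate (SE), power | 30% of pilot changes: estimate (SE), power |
|---|---|---|
| 0% | 0.01 (0.31), 0.05 | 0.00 (0.13), 0.05 |
| 25% | 0.07 (0.32), 0.06 | 0.07 (0.14), 0.10 |
| 50% | 0.16 (0.31), 0.08 | 0.16 (0.14), 0.21 |
| 100% | 0.29 (0.31), 0.16 | 0.29 (0.13), 0.59 |

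The last row shows that adjustment costs power even when none of the effect runs through waits.

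**ED volume in the primary model.** This was checked separately, assuming a direct LOS effect of −30 minutes, baseline volume 100 and 0.5 minutes of LOS per unit of volume. If SurgeCon does not change volume, the adjusted and unadjusted estimates are both −30.1. If it raises volume by 5, 10 or 25.7 units, the unadjusted (total) estimates are −27.4, −24.9 and −17.0, while the adjusted estimate stays near −30. If it lowers volume by 10, the unadjusted estimate is −35.1 and the adjusted one −30.0.

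**The case against.** **The effect is not wholly removed.** A reader might infer that the satisfaction effect is adjusted away altogether. The article does not support that. The environment component and the reorganised staff communication in Table 1 can raise satisfaction without shortening waits, and that part stays in the coefficient. This objection stands: only the part that runs through waiting is lost.

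**The size is assumed.** Nothing in the article informs the mediated share, and 0.265 SD is not a protocol figure. The 29% and 11% hold the unadjusted SE fixed, so they are ceilings, not the power of the specified model. Unmeasured causes of both waits and satisfaction, such as the staffing shortages under Impact of COVID-19, could also bias the adjusted coefficient in either direction. All of this stands, and the figures are illustrative only. None of it makes the coefficient a total effect.

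**The covariates' timing is not stated.** If they were fixed pre-trial values, they would not be mediators. That is possible, but the article defines these indicators only as monthly measures over the study period.

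**ED volume.** A reader might infer that the primary model repeats the error, since "ED setting (rural or urban), ED volume, and size of ED administrative resource will be added as cluster-level covariates". The article does not support this. Study Population treats volume as a driver of the indicators ("LOS, PIA, and LWBS because they are impacted by patient volume"). Background reports the pilot gains as occurring despite a 25.7% rise in volume and does not attribute the rise to SurgeCon. The timing of the volume covariate is not stated. If volume is external, adjusting for it causes no bias. If SurgeCon raises volume, the adjusted result overstates the delivered benefit and does not remove it. Volume adjustment may also help against the pandemic demand shifts the article describes. One limited point remains: Data Collection and Monitoring plans to assess the intervention's "impact on the type and volume of patients who visit one of the 4 selected ED sites", so an effect on volume is left open.

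**Conclusion.** The point holds for the satisfaction and patient-experience model. As specified, its intervention coefficient excludes the effect that passes through LOS, PIA and LWBS and does not estimate the impact named in the secondary objective. This follows from the article's own text and needs no numerical assumption beyond reading the indicators in their monthly form.

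The size does rest on assumptions. For a total effect that would have 80% power, power for the remaining effect is at most about 29% if half runs through waits and 11% if three quarters does, and lower once the SE is inflated. In the simulation the SE roughly tripled at pilot-sized indicator changes (0.10 to 0.31) and rose to about 0.13 at 30% of them.

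The conclusions on LOS, PIA and LWBS do not depend on this. ED volume in the primary model is not the same error and warrants at most a sensitivity analysis.

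**What to change.** - In Analyses, remove cluster-level LOS, PIA and LWBS from the main satisfaction and experience model. Keep age, gender and reason for visit.
- If the indicator-adjusted model is wanted, report it as a labelled exploratory mediation analysis. State that its coefficient is the effect not passing through waits and that it assumes no unmeasured common causes of waits and satisfaction.
- For LOS, PIA and LWBS, state whether the ED volume covariate is baseline or concurrent. If it is concurrent, add a sensitivity analysis without it. Keeping concurrent volume in the main model is defensible, given the pandemic-related changes in demand.

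The cost is a few sentences of analysis wording and one extra model run. No new data are needed and the sample size does not change.

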#### Analytical Considerations

In the basic model suggested by Hussey and Hughes [43], a homogeneous secular trend is assumed across all clusters. However, this SW-CRT has numerous methodological difficulties such as confounding with time, time-varying correlation structure, change in treatment effect over time, within-cluster contamination, and change in design variation. These complexities differ according to the way SW-CRTs are designed. A summary of key methodological issues that need extra consideration when reporting SW-CRT is presented in Table S2 in Multimedia Appendix 1. We will be continuously monitoring and intervening when necessary to manage analytical challenges associated with this kind of design. Any unexpected event during the study period will be recorded, and methodological approaches to overcome the issue will be described in the reports.

### Patient Engagement

As a patient-oriented study, the inclusion of patients in the research team is critical. An example of this is our lead patient research partner who has been advising the research team since the pilot study. The research team is also advised by the patient engagement working group, which comprises the lead patient partner, scientific patient engagement lead, clinicians, researchers, and students. We designed the protocol to give patients a variety of opportunities to participate in research activities. Applicable research activities vary in terms of the level of engagement required (eg, surveys vs full-team membership). We are currently recruiting additional patient research partners for the study’s patient engagement working group, but patients can also be involved in other committees and working groups suited to their interests and needs. Overall, the level of engagement will vary from receiving information to consultation to full collaboration with patient partners to inform all project activities. We used 4 essential pillars, as suggested by Shippee et al [49], to inform our patient engagement strategy, which is further described in our implementation protocol [24]. We are committed to upholding the guiding principles of inclusiveness, support, mutual respect, and cobuilding inherent in these pillars.

### Impact of COVID-19

The impact of the COVID-19 pandemic on the study and its protocol is ongoing. Public health care measures such as stay-at-home orders, handwashing, and physical and social distancing compounded with COVID-19 concerns have caused rapid disruptions in daily life and a delay in the implementation of the intervention. A notable effect may be a significant change in the number of patients visiting EDs. The fear that the public is experiencing because of COVID-19 is likely exacerbated by measures related to stay-at-home orders, self-isolation protocols, including quarantines, travel restrictions, and closures of nonessential businesses. With most of Newfoundland and Labrador’s residents practicing social distancing and self-isolating and an increase in the number of workers who are now working remotely, the potential for injuries such as trauma due to motor vehicle collisions may decline considerably [50]. Given the potential reduction in injury and the climate of fear at the beginning of the COVID-19 pandemic, patients were found to be less likely to use hospital ED services [51]. Another impact of the pandemic is the temporary suspension of essential and nonessential medical procedures. The suspension of certain health care services may have downstream effects on wait times because delays in surgeries and other important medical procedures could increase the number of higher acuity patients who develop complications because of the delay. These higher acuity patients require additional resources and time and can have a significant impact on patient flow and wait times. Other pandemic-related considerations include added wait times because of public health measures such as increased handwashing, social distancing, donning and doffing of personal protective equipment, and sanitizing high-touch surfaces. More recently, a transition from in-person to web-based or telephone family physician consultations may be increasing ED patient volumes [52,53]. The pandemic has also exacerbated issues related to physician and nursing shortages in the province [54-56]. As a result, achieving optimal sample size from each of the ED sites might be compromised because of pandemic-related ED service use trends. The research team will look to explore the effects of the COVID-19 pandemic on patient flow and wait times in EDs.

### Description of Intervention

Our intervention comprises several components that will be implemented sequentially. The SurgeCon intervention is a pragmatic ED management platform that includes 3 distinct intervention components that together act to improve ED efficiency, patient satisfaction, and the value of emergency service costs (Table 1). SurgeCon’s intervention process starts with a site assessment during the transition period that aims to clarify key performance issues, collect information related to the ED’s organizational and workflow structures, and prepare ED staff and management for upcoming operational changes, while also establishing a patient-centered ED environment and action-based ED management (Figure 3). Due to the high degree of variability that exists between EDs, the information collected during the site assessment allows for the customization of SurgeCon’s underlying protocols and determines whether certain components of the intervention are appropriate or applicable for implementation. A site assessment will be conducted by members of our working group who developed SurgeCon in Carbonear. The implementation working group will follow a 4-step protocol for these site assessment visits; for further details please see the implementation protocol [24].

**Figure 3 figure3:**
[figure not shown]
The SurgeCon intervention logic model. ED: emergency department; LOS: length of stay; LWBS: leaving the emergency department without being seen; PIA: physician’s initial assessment; PREM: patient-reported experience measure.

**Table 1 table1:** Intervention components and their associated action plans.

Intervention components and action plans		Description and strategy
**Restructure ED^a^ organization and workflow**		
	Stable patient priority setting	Canadian EDs have been using the CTAS^b^ since 1999 [57]. What the SurgeCon intervention proposes is to augment CTAS by combining CTAS scores and waiting times to best meet the suggested time frame set out by the CTAS organization. Patients who are CTAS level 1 (resuscitation) or 2 (emergent) who are not stable will still be treated immediately in this model, but individuals who are less urgent (CTAS 3-5) will be treated when the CTAS 1-2 individuals become more stable, but before they are discharged. This allows the physician to quickly treat and discharge less urgent individuals before returning to spend more time with the urgent cases. This prioritization method can significantly improve patient flow without having to compromise patient safety.
	Door-to-door focus	A number of studies have found a strong correlation between patient satisfaction and PIA^c^; the shorter the PIA, the more satisfied the patient [58,59]. To reduce the time to PIA, we will use the following strategies: ED physicians and frontline providers will triage with nursing staff with the goal of increased patient discharge from the fast-track area or triage room without waiting. Triage nurse–driven orders (eg, symptom management, laboratory testing, and diagnostic imaging) will only be applied on patients who would be waiting longer than 1 hour to see a physician. If the patient can be seen by a physician within an hour, waiting for potentially unnecessary test results could delay the PIA. ED physicians will review patients arriving on ambulance stretchers in the hallway if there are no available beds instead of waiting for a bed to be free.
	Nurse practitioner–physician communication	SurgeCon reorganizes the traditional Canadian ED communication structure by promoting communication between NPs^d^, ERPs^e^, and RNs^f^ to work collaboratively to improve patient flow through appropriate allocation of patients. By opening lines of communication between NPs, ERPs, and RNs, the entire ED can work in unison to move patients further along their path to being discharged.
